**LIST OF ABBREVIATIONS**

A-Sync Alpha-synuclein

CFU Colony Forming Unit

GTT Gatrointestinal Transit Time

HLS Hard and Lumpy stool

MDS Movement Disorder Society

NMS Non-motor Symptoms

PD Parkinson Disease

PDQ39 39-Parkinson’s Disease Questionnaire

SCFA Short Chain Fatty Acids

SPSS Statistical Package for the Social Sciences Software

UPDRS Unified Parkinson’s disease Rating Scale

GQ Garrigues Constipation Questionnaire

**INTRODUCTION**

Constipation is one of the commonest non motor symptoms (NMS) in Parkinson Disease (PD) and reported in approximately 80-90% of patients ^1-3^. The NMS occur throughout the stages of PD, and some even predate the development of motor symptoms by 5-10years^4^. Constipation and digestive issues in PD are due to multifactorial factors contributed by the enteric and central nervous system dysfunction, side effects of medications and natural process of ageing. Besides, dystonia of the striated external sphincter and the reduction of dopamine containing neurons in the enteric nervous system also contributes towards the development of gastrointestinal symptoms in PD ^5^. A study by Azmin et al^6^ shows that NMS prevalence was as high as 97.3% in patients with idiopathic PD of which gastrointestinal symptoms were the commonest affecting 76.1% of patients. In general, constipation is diagnosed by the reporting of multiple symptoms such as infrequent BMs, production of hard or lumpy stools (HLS), incomplete evacuation, straining, abdominal discomfort or pain, and bloating. The management of constipation remains challenging. Bulking agents, osmotic laxatives, stimulant laxatives, and stool softeners are commonly used with most of the patients adopt self-management approaches with 80% trying over the counter product ^7^ such as foods believed to exert a laxative effect, “functional foods,” and nutraceuticals ^8^.

Recent studies showed that alpha-synuclein (a-Sync) aggregation in colonic mucosal of PD patients leads to disruption of intestinal barrier integrity and causes constipation^9^. Alpha-synuclein is a primary structural component of Lewy bodies (protein clumps) and has been shown to play role in sporadic/familial PD. More recently, studies have shown that there is a gut dysbiosis with alterations in fecal microbial composition among PD patients which also contributes toward constipation in PD. This gut dysbiosisis is believed to cause neuroinflammation leading to a-Sync misfolding in the colonic mucosal of PD patients.

A recent study by Keshavarzian et al^10^ compared colonic bacterial composition among PD patients and healthy controls utilising sigmoid mucosal biopsies and fecal samples. Fecal and mucosal associated microbiota composition were characterized using highthroughput ribosomal RNA gene amplicon sequencing and it was found that there were significant differences at all taxonomic levels in fecal and mucosal associated microbiota communities between PD patients and control. Anti-inflammatory butyrate producing bacteria from the genera *Blautia, Coprococcus,* and *Roseburia* were signiﬁcantly less abundant in PD fecal samples compared to control which could potentially have caused intestinal inflammation and barrier dysfunction ^11-12^ and possibly the aggregation alpha-Sync protein in colonic mucosal.

Another study on SCFA concentrations and microbiota composition by M.M. Unger et al^13^ in fecal samples of 34 PD patients and 34 age-matched controls, showed that fecal samples from PD patients had low concentration of short chain Fatty Acid (SCFA). The study also showed that SCFA bacterial *phylum Bacteroidetes* and the bacterial family *Prevotellaceae* were reduced but *Enterobacteriaceae* (Gram Negative Bacilli) were more abundant in fecal samples from PD patients compared to matched controls. Therefore it was suggested that the reduction in SCFA induced alteration in enteric nervous system contributing to gastrointestinal dysmotility^14^.

Forsyth et al^14^ reported an increased intestinal permeability in PD that correlated with staining for E. coli (a bacterial species assigned to the family *Enterobacteriaceae*) and concluded that a compromised intestinal barrier might help to expose the enteric nervous system to noxa in PD . Hence, the observed increased abundance of *Enterobacteriaceae* might be pathophysiologically relevant for gastrointestinal dysmotility in PD.

There are several types of SCFAs produced by metabolic activities of intestinal bacteria, including acetic, propionic, butyric, and lactic acids ^15^. Of these SCFAs, butyrate and lactate are of particular importance in mechanisms of constipation. Butyrate has been shown to have anti-inflammatory properties and is involved in many cellular processes such as repair of the gut mucosal lining, stimulation of the autonomic nervous system and production of hormones associated within the GI tract ^16^. Besides butyrate, lactic acid is another important SCFA produced by intestinal bacteria such as *lactobacilli, bifidobacteria, enterococci, streptococci and Eubacterium*^17^. Lactate in colonic mucosal is normally used by other butyrate-producing bacteria as a precursor to synthesis butyrate products^18^.Based on the role of SCFA-butyrate organism in colonic mucosal and the evidence of low abundance of butyrate producing organism in PD patients, there is a potential role for probiotics in correcting the imbalance of intestinal bacterial (dysbisosis) and enhancing the number of this good microbiota in improving digestive symptoms.

**LITERATURE REVIEW**

Probiotics are live microorganism that are able to promote healthy digestive tract and immune system and the benefits are widely studied at this time. When probiotics are administered in adequate amounts, it gives health beneﬁt to the host^19^. There are several potential mechanisms of action by which probiotics may beneﬁt functional constipation^20^. First, probiotics modify the gastrointestinal microbiota, which is known to be altered in constipation^21 -22^. Second, probiotic metabolites may alter gut function, including sensation ^23-24^ and motility ^25-26^. Third, some probiotics increase the production of lactate and short-chain fatty acids, reducing luminal pH, which some researchers have proposed will enhance colonic peristalsis and shorten whole gut transit time (GTT) ^27-28^.

A randomised double blind, placebo-controlled trial study on efficacy of probiotics and prebiotics in Parkinson disease with constipation by Michela et^29^ al showed that PD with constipation who consumed fermented milk containing multiple probiotic strains and prebiotic fibre increase the number of complete bowel movements significantly. In this study, patients were randomly assigned to either fermented milk, containing multiple probiotic strains (*Streptococcus salivarius subsp thermophilus, Enterococcus faecium, Lactobacillus rhamnosus GG, Lactobacillus acidophilus, Lactobacillus plantarum, Lactobacillus paracasei, Lactobacillus delbrueckii subsp bulgaricus, andBifidobacterium )* of 250x 10^9^ colony forming unit (CFU) and prebiotic fibre, or placebo, once daily for 4 weeks. The above findings support the theory that manipulation of gut microbiota maybe a therapeutic option for functional bowel disorders^17^.The study also showed that probiotic mixture with prebiotics had greater efficacy than single strains in assisting complete bowel movement in Parkinson disease, although it is not clear whether this was attributable to synergism or the consequence of the higher probiotic dose used in the study^30^.

A systematic review and meta-analysis of randomized controlled trials in unselected populations of patients with functional constipation demonstrated that the use of probiotics has substantial benefits in stool frequency, transit time and stool consistency with favourable beneficial effects of *B. lactis* strain in particular^31^. The results of this study indicate that, overall, probiotics positively affected all of these measures. Besides, several other cardinal symptoms of constipation also significantly improved for example symptoms such as bloating, sensation of incomplete evacuation, occurrence of hard stools, and ease of stool expulsion.

An open-label, randomized, controlled study by T.Sakai et al^32^ using daily intake of fermented milk for 3 weeks demonstrated that daily consumption of fermented milk containing *Lactobacillus casei strain Shirota (LcS)* significantly reduced the incidence of hard or lumpy stool by 50% in healthy subjects with moderate to severe constipation compared to placebo.

Considering the high prevalence of constipation among PD patients and the positive effects on probiotics alleviating constipation, we attempt to explore the effects of probiotics in PD patients with constipation compared to placebo. We hypothesize that probiotics may be able to partially correct the gut dysbiosis that occurs in PD and improve quality of life among PD patients.

**3. THESIS STATEMENT**

**3.1 RESEARCH QUESTION**

- Are probiotics effective in improving constipation in PD patients?

**3.2 RESEARCH HYPOTHESIS**

- Probiotics consumption improves constipation , shorten Gut Transit Time(GTT) and improve constipation-related symptoms and Quality of life

**4. OBJECTIVE**

**4.1 PRIMARY OBJECTIVE**

- To determine the effects of probiotics (multistrains of Lactobacillus and Bifidobacterium ) on constipation among Parkinson disease patients compared to placebo
- To determine the effects of probiotics on Gastrointestinal Transit Time (GTT) compared to placebo

**4.2 SECONDARY OBJECTIVE**

- To determine the effects of probiotics on overall quality of life compared to placebo
- To determine the effects of probiotics on disease severity and non-motor symptoms score.

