|  | **6. HOSPITAL PROFILE/DEMOGRAPHIC**  **7. STUDY PERIOD**  June 2018 – June 2019  **8. SUBJECTS**  **8.1 TARGET POPULATION**  Patients with Parkinson disease attending the neurology outpatients clinic who fulfil inclusion and exclusion criteria  **9. SAMPLING**  **9.1 INCLUSION CRITERIA**   1. Idiopathic PD diagnosed using UK PD Society Brain Bank Criteria 2. Diagnosis of constipation according to Rome III Functional Constipation Criteria 3. Written informed consent   **ROME III Diagnostic Criteria : Functional Constipation**   \| Functional Constipation \| \| --- \| \| Must include 2 or more of the following:  Straining *  Lumpy or hard stools*  Sensation of incomplete evacuation*  Sensation of anorectal obstruction/blockage*  Manual manoeuvres to facilitate defecation(digital evacuation, support of pelvic floor)*  <3 defecation per week*  ***≥25% of defecations**  Loose stool rarely present without use of laxatives  Insufficient criteria for IBS \|   Based on Longstreth GF et al.Gastroenterology 2006 ;130:1480-1491  **9.2 EXCLUSION CRITERIA**   1. Secondary Parkinsonism 2. Previous history of small and large bowel disease 3. Previous extensive gastrointestinal tract surgery 4. Positive stool occult blood in the last 1 month 5. Use of probiotics or antibiotics in 2 weeks before baseline visit 6. Underlying Dementia 7. Hypothyroidism 8. Diagnosed with major depression and on antidepressant 9. Lactose intolerance   10. Type 1 and Type 2 DM  **10. DATA COLLECTION**  **10.1 METHOD OF DATA COLLECTION**  Patients with idiopathic PD attending the neurology outpatients’ clinic will be invited to participate in the study. All subjects will be screen for constipation by using Rome III Criteria – Constipation Module. Written informed consent will be obtained from all subjects after screening inclusion and exclusion criteria. Baseline demographic data will be recorded into a structured questionnaire.  Screening assessment :  1) Constipation screening using Rome III Criteria – Constipation Module  2) Fecal occult blood testing - negative test will be included in the study  The eligible subjects will be assess on the first visit as below :  1) Constipation symptoms by using Garrigues Constipation module (GQ)  2) Quality of life by using PDQ39 Questionnaire (self-administered malay version )  3) Parkinson Disease severity by using MDS-UPDRS  4)Non motor symptoms of PD by using NMS scale  (All the above questionnaires are validated)  Subsequently, subjects will be instructed to consume 4 red carmine capsule(food colourant) and once the stool turn red in colour, Gatrointestinal Transit Time(GTT) will be measured and recorded. Subjects will then receive a 3g sachet of either probiotics (containing multistrains of lactobacillus and Bifidobacterium 30 Colony Forming Unit) or placebo twice-daily for a duration of 8 weeks. Once consumption completed, subjects need to consume again another 4 red carmine capsule and GTT will be measured and recorded again. Final assessment will be done once subjects completed all the probiotics or placebo given(week 8) and subjects need to be assess again on constipation symptoms, non-motor symptoms, quality of life and disease severity same as done at baseline using the same questionnaire.  **10.2 STUDY PROTOCOL**  Randomization  All patients who fulfill inclusion and exclusion criteria will be stratified based on age, sex and background social economics. Patients who are enrolled will be randomized into two treatment groups which a probiotics group who will receive probiotics (containing multistrains of lactobacillus and Bifidobacterium 30 Colony Forming Unit) or placebo using blocks randomization method, in blocks of 4. Patients and investigator will remain blinded to the treatment protocol.  Following randomization, patients will receive their assigned treatment from the pharmacy department, Hospital Canselor Tuanku Muhriz, PPUKM  Treatment  Active treatment group will receive a 3 gram sachet of probiotics containing multistrains of lactobacillus and Bifidobacterium 30 Colony Forming Unit x 10^9^ to be taken twice daily for 8 weeks.  Composition of probiotics:   \| Lactobacillus acidophilus \| 107mg \| \| --- \| --- \| \| Lactobacillus casei \| 107mg \| \| Lactobacillus lactis \| 107mg \| \| Bifidobacterium bifidum \| 107mg \| \| Bifidobacterium infantis \| 107mg \| \| Bifidobacterium longum \| 107mg \|   Placebo group will receive a 3g sachet of substance (powder form) that has no therapeutic effect to be taken twice daily for 8 weeks.  All test products will be concealed in sealed envelopes, to ensure blindedness  **10.3 STUDY ASSESSMENT**  All patients will be assessed at baseline and week 8 for improvement in constipation symptoms using the Garrigues Constipation Questionnaire^35^, Quality of Life by using self- administered PDQ39 questionnaire (malay version)^36^, disease severity by using MDS-UPDRS and non-motor symptoms by using NMS scale . The Gastrointestinal transit time will be assessed at baseline and week 8 using red carmine capsule. Compliance to treatment, side effects and clinical assessments will be performed by a blinded assessor at baseline and week 8 for both groups.  **Gastrointestinal Transit Time Protocol**  Following randomization, subjects will be instructed to ingest 4 red carmine capsule after last bowel opening. Red carmine capsule is a food colorant and non-toxic to body which is used to measure GTT. The time of ingestion will be recorded. GTT is measured from the time of red carmine capsules consumption and first appearance of red colored stool. The duration from time of ingestion and appearance of red colored stool (Gastrointestinal transit time) will be recorded by patient at baseline, and week 8. The use of laxatives is not forbidden, but patients are required to use as per needed. GTT was measured during pre and end treatment in both groups.  **Constipation-Related Symptom Assessment**  Constipation related symptoms will be assessed using the Garrigues Constipation Questionnaire (GQ)^35^ which is a 21-item that was developed to define the presence of chronic constipation. Only 13 of the 21 items are related to bowel habits. The Rome 111 criteria were used to define constipation. The items are scored using two different four-point Likert scales. The first consisted of ‘never’, ‘sometimes’ (25% of the time) and ‘always’. The second consisted of ‘never’, ‘fewer than once a week’, ‘one or more times a week’ and ‘every day’. Total and cut off scores were not reported.  **Quality Of Life Assessment**  Baseline Quality of life patients will be assess using self-administered PDQ-39^36^ Questionnaire(Malay version) and end of intervention, subject will be assessed again using the same questionnaire. PDQ-39 questionnaire contains 39 items with each item was rated by the patients using one of five categories, from 0 (never) to 4 (always). PDQ-39 summary index (PDQSI) is calculated by dividing the sum of the total raw score by the maximum possible score (156 or 152 points, depending on the patient’s marriage status) and multiplying by 100. In this study, we will use PDQSI as a standardized index for representing PD patients’ life quality.  **Non Motor symptoms (NMS) assessment**  Severity of Non Motor symptoms of each individual will be assess using NMSS Questionnaire. Frequency and severity of each NMS are taken into account. Final total score of disability (0=no disability; 360=maximal disability).  **DDisease severity assessment**  Parkinson Disease severity assessment will be assess using MDS-UPDRS questionnaire. MDS UPDRS has four parts which include nonmotor experiences of daily living (13 items), motor experiences of daily living (13 items), motor examination (18 items), and motor complications (six items). Each subscale now has 0-4 ratings, where 0 = normal, 1 = slight, 2 = mild, 3 = moderate, and 4 = severe.  10.4 **VALIDITY OF TOOLS**  NMS and MDS-UPDRS are public domain questionnaire  Validated score : PDQ 39 (malay version)- permission obtained from author  Garrigues Constipation Questionnaire- awaiting permission from author  **11. STASTICAL ANALYSIS**  Statistical Package for the Social Sciences (SPSS) Software version 2 will be used for statistical analysis. Age, height, weight, body mass index (BMI) and gender were compared between the groups by Student’s t-test and the chi-squared test. General Linear Model will be used to compare intestinal transit time in probiotics and placebo groups before and after 8 weeks of intervention. Pre- and post-probiotics consumption data on clinical evaluation of constipation that will be obtained from all the questionnaires namely Rome III criteria, PDQ-39 Questionnaire and Garrigues Constipation Questionnaire will be analysed using Mc Nemar Test. Independent t-test will be used to compare the differences of intestinal transit time in both groups. Pearson correlation and Simple linear regression analysis will be utilized to explore the relationship and effect between two numerical variables. A p-value <0.05 will be considered as statistically significant.  **11.1 SAMPLE SIZE CALCULATION**  The sample size is being calculated based formula comparing between two proportions. Sample size calculation was performed according to a study by Sakai et al^32^ based on value reported on changes in percentage of bowel movements and complete bowel movements after 3 weeks of probiotics treatment where there was a significant decreased from 73.7% to 36.8%,  Formula for sample size comparing two proportions:  [figure not shown]  Sample size was estimated as follows :  p1 = 0.737  p2 = 0.368  zα = 1.96  zβ = 0.84  n = 0.737 (1 – 0.737) + 0.368 (1 – 0.368 ) X (1.96 + 0.84) ^2^  (0.737 – 0.368) ^2^  n = 0.193831 + 0.232576 X 7.84  0.136161  n = 25 per group  The number of samples per group is further added 20% to compensate for non-response and lost to follow up. The final samples required for each group is 30 patients. |

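### MDS-UPDRS and NMS have an objective but no placebo contrast and no stated analysis, and the only questionnaire method in section 11 is before/after, so a benefit could be claimed from an uncontrolled change

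*Combined protocol and SAP*

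**What the plan says.** Sections 4.1 and 4.2 list four objectives. Both primary objectives (constipation and gastrointestinal transit time) name placebo as the comparator, and so does the first secondary one: "To determine the effects of probiotics on overall quality of life compared to placebo". The second secondary objective stops short of that: "To determine the effects of probiotics on disease severity and non-motor symptoms score".

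Section 10.3 has PDQ-39, MDS-UPDRS and NMS assessed at baseline and week 8 in all patients. It commits to one PDQ-39 summary index (PDQSI) and gives NMS one total from 0 to 360. For MDS-UPDRS it only describes the instrument, beginning "MDS UPDRS has four parts which include nonmotor experiences of daily living (13 items), motor experiences of daily living (13 items", and then lists the motor examination and motor complications parts. No total and no lead part is chosen.

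Section 11 takes pre- and post-consumption data from the questionnaires, "namely Rome III criteria, PDQ-39 Questionnaire and Garrigues Constipation Questionnaire will be analysed using Mc Nemar Test". MDS-UPDRS and NMS are not in that list. The between-group outcome methods, a General Linear Model and an independent t-test, are named only for transit time. Correlation and simple linear regression are mentioned in general terms and tied to no objective. One rule covers every test: "A p-value <0.05 will be considered as statistically significant".

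**The concern.** The trial randomises to placebo and collects these scales in both arms, so the valid contrast is available. The written analysis does not use it. McNemar's test compares paired binary responses within the same patients and says nothing about the difference between arms. No cut-off is given that would make PDQSI binary, so even quality of life, whose objective names placebo, has no arm comparison in section 11. For MDS-UPDRS and NMS nothing is stated, and an analyst looking for a precedent in the plan finds only the before/after one.

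A fall in score from baseline to week 8 in the probiotic arm mixes any probiotic effect with placebo response, repeat-rating effects and regression to the mean. Because no MDS-UPDRS score is fixed, the part that moved most could also be chosen after the data are seen. What is at stake is a claim that probiotics improve Parkinson severity, non-motor burden or quality of life when the placebo arm changed just as much.

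**Working it through.** **Inputs from the documents (section 11 and 11.1).** Significance threshold 0.05, taken as two-sided because the sample-size formula uses z = 1.96. Proportions 0.737 and 0.368, zβ = 0.84.

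**Reproducing the plan's sample size.** [0.737 × 0.263 + 0.368 × 0.632] × (1.96 + 0.84)² / (0.737 − 0.368)² = 0.426407 × 7.84 / 0.136161 = 24.55, rounded up to 25 per group. Then 25 × 1.2 = 30, which agrees with "The final samples required for each group is 30 patients". The two sizes used below are therefore 30 (full retention) and 25 (the number before the allowance for loss). The plan states no error rate for the secondary outcomes, so there is no such figure to reproduce.

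**Which outcomes have what.**

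| Outcome | Objective names placebo | Deciding score | Analysis in section 11 |
|---|---|---|---|
| PDQ-39 | yes | PDQSI | pre/post McNemar |
| NMS | no | total, 0–360 | none |
| MDS-UPDRS | no | none | none |

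**Before/after route.** Assume both arms improve by δ, in SDs of the change score, with no probiotic effect. The within-arm paired t statistic is noncentral t with n − 1 degrees of freedom and noncentrality δ√n. Benefit is declared when it exceeds the upper 2.5% point of the central t distribution in the favourable direction.

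| Assumed δ | δ√30 | P(benefit declared), n = 30 | δ√25 | P(benefit declared), n = 25 |
|---|---|---|---|---|
| 0 | 0 | 2.5% | 0 | 2.5% |
| 0.2 | 1.10 | 18.4% | 1.0 | 15.9% |
| 0.3 | 1.64 | 35.5% | 1.5 | 30.2% |
| 0.4 | 2.19 | 56.3% | 2.0 | 48.4% |

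In a between-arm comparison the expected difference is δ − δ = 0, so the false-benefit rate stays at about 2.5% per test whatever the shared drift.

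**Several between-arm tests.** Suppose the arms were compared on k scores, each at two-sided 0.05. Three tests would be PDQSI, NMS total and one MDS-UPDRS score. Six would be PDQSI, NMS total and all four MDS-UPDRS parts. Under independence, P(at least one false benefit) = 1 − 0.975^k and P(at least one false result in either direction) = 1 − 0.95^k. For correlated tests, 1,000,000 draws of equicorrelated normal statistics were simulated.

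| k | Correlation | At least one false benefit | At least one false result, either direction |
|---|---|---|---|
| 3 | 0 | 7.3% | 14.3% |
| 3 | 0.5 | 6.3% | 12.5% |
| 3 | 0.8 | 4.9% | 9.8% |
| 6 | 0 | 14.1% | 26.5% |
| 6 | 0.5 | 10.3% | 20.7% |
| 6 | 0.8 | 7.0% | 13.9% |

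**The case against.** The strongest reply is that the comparison with placebo is implied. Section 5.1 describes a randomised, double-blind, placebo-controlled trial, and section 10.3 has a blinded assessor perform clinical assessments in both groups at both visits. That stands as a reading of intent. A reader might infer that the plan commits to a before/after analysis of MDS-UPDRS and NMS. It does not; it states no analysis for them. But design does not supply an estimator, and the one questionnaire method that is written down makes no arm comparison.

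The drift of 0.2 to 0.4 SD is assumed, and the plan names no paired t-test. Both points are correct. The percentages show how fast the error grows; they do not forecast this trial. Full retention is also optimistic, given "The number of samples per group is further added 20% to compensate for non-response and lost to follow up", which is why n = 25 is shown as well.

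A reader might also infer a 13–21% chance of a false secondary benefit. The documents do not support that. The figure counts false results in either direction, for 3 to 6 between-arm tests at an assumed correlation of 0.5, and the plan does not propose testing all four MDS-UPDRS parts. Nor can it be said that the whole severity and non-motor objective lacks a deciding score, because NMS has a defined total.

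Finally, these outcomes are already labelled secondary in a 60-patient trial, so formal multiplicity control is a matter of preference. That is accepted. Quality of life also appears in the research hypothesis of section 3.2 ("improve constipation-related symptoms and Quality of life"), but section 4.2 classes it as secondary, so moving it is not needed.

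**Conclusion.** The point holds as a gap in specification with a real consequence. The severity and non-motor objective names no placebo contrast, MDS-UPDRS and NMS have no analysis, MDS-UPDRS has no deciding score, and the only stated questionnaire analysis cannot separate probiotic from placebo response.

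If an uncontrolled before/after change were used, the chance of declaring a benefit that does not exist would be about 18%, 36% or 56% with 30 patients in the arm, and 16%, 30% or 48% with 25. This assumes shared improvements of 0.2, 0.3 or 0.4 SD of the change score, a paired t-test and no probiotic effect.

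Multiplicity is the lesser part. Across 3 to 6 between-arm tests the chance of at least one false benefit is about 6–10% at an assumed correlation of 0.5, and 5–14% over correlations from 0.8 to 0, against 2.5% for one test. The number of tests and the correlation are assumptions, not figures from the documents. The change should be made, but it does not touch the two primary objectives.

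**What to change.** 1. **Section 4.2:** name placebo as the comparator in the second objective, as the other three do.
2. **Section 11:** analyse NMS total, PDQSI and one MDS-UPDRS score as the week-8 probiotic-minus-placebo difference adjusted for the baseline value (for example by analysis of covariance), with a 95% confidence interval. Name the MDS-UPDRS score before unblinding and report the remaining parts descriptively. Remove PDQ-39 from the McNemar sentence, or keep that test only as a within-arm description.
3. **Section 11:** state that these outcomes are secondary and supportive. Formal adjustment is optional; if significance claims are wanted, a Bonferroni split over three scores would be 0.05/3 = 0.0167 each.

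The cost is a few sentences, with no new data, visits or patients, because both arms already complete these scales at both visits. The downside is that a before/after change, or an isolated secondary p-value just under 0.05, could no longer be presented as a probiotic effect.
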